#### Data acquisition parameters

2.6.3

The system monitor the signal quality in real time with automatic adjustments for probe contact optimization. The source-detector channel configurations cover bilateral prefrontal regions, including the dorsolateral prefrontal cortex (dlPFC), ventrolateral prefrontal cortex (vlPFC), and anterior prefrontal cortex (aPFC) regions.

Behavioral data from cognitive tasks is recorded synchronously with fNIRS signals, including response accuracy, reaction times, and response patterns. Task timing and event markers are automatically integrated with the fNIRS data stream to enable precise hemodynamic response analysis.

#### Outcome measures and analysis framework

2.6.4

The primary fNIRS outcome measures were designed to capture task-related activation and intrinsic functional connectivity.

*Task-evoked activation*: Hemodynamic responses during cognitive tasks will be quantified as changes in the HbO_2_ concentration relative to the pre-task baseline. Task-specific activation patterns will be calculated for each cognitive domain (working memory and cognitive inhibition) and will be compared between insomnia and control groups.

*Resting-state functional connectivity*: Functional connectivity will be assessed by calculating Pearson correlations between HbO_2_ time series from different prefrontal regions during both pre- and post-task resting periods. Network topology measures, including node strength and clustering coefficients, will be derived to characterize the prefrontal network organization.

*Hemispheric asymmetry indices*: Lateralization of prefrontal function will be quantified using asymmetry indices by comparing left- and right-hemisphere activation and connectivity patterns. These measures provide insight into the potential hemispheric imbalance associated with insomnia.

*Cognitive performance-brain activity relationships*: Correlations between behavioral performance measures (accuracy, reaction time) and concurrent brain activation will be calculated to examine brain-behavior relationships and identify potential compensatory mechanisms in insomnia.

The fNIRS protocol will be specifically designed to be integrated with a broader deep phenotyping framework, with derived neural metrics to serve as features in computational analyses alongside clinical, digital, and genomic data to identify neurophysiological correlates of insomnia phenotypes.

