#### fNIRS system and setup

2.6.1

A portable multichannel fNIRS device (NIRSIT, OBELAB Inc., Seoul, Republic of Korea) is used to record the prefrontal hemodynamic responses. The system employs near-infrared light at dual wavelengths (760 and 850 nm) to measure the changes in oxygenated (HbO_2_) and deoxygenated (HbR) hemoglobin concentrations. The device features a flexible probe configuration optimized for prefrontal cortex coverage with source-detector separations of 30 mm to ensure adequate cortical sensitivity.

All fNIRS assessments are conducted at the Korea University Anam Hospital by trained research personnel, following standardized protocols. The session room maintained at a comfortable temperature and lighting conditions to minimize environmental confounding factors. The participants are seated comfortably with the fNIRS cap positioned according to the international 10–20 system, ensuring consistent probe placement across participants.

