#### Preliminary data analysis and quality control

2.8.1

Data preprocessing: All datasets will undergo comprehensive quality-control procedures. Digital phenotyping data will be screened for outliers using interquartile ranges and temporal consistency checks. The clinical assessment data will be examined for completeness and consistency. fNIRS data undergo standard preprocessing, including motion artifact correction and signal quality assessment. Genomic data quality control will follow the established GWAS protocols.

*Missing data strategy*: Clinical and self-report variables will be handled using multiple imputation by chained equations (MICE) under the Missing at Random (MAR) assumption. For digital phenotyping data with systematic missingness (e.g., device non-wear periods), short-term gaps will be interpolated using Kalman smoothing to preserve temporal continuity, whereas longer missing periods will be excluded from time-series analyses. Sensitivity analyses will assess the impact of missing data assumptions on the primary findings.

*Descriptive statistics:* Comprehensive descriptive analyses will characterize both cohorts across all measurement domains. Continuous variables will be summarized using mean, standard deviation, median, and interquartile ranges. Categorical variables will be presented as frequencies and proportions. Data distributions will be assessed using histograms, Q-Q plots, and normality tests to inform subsequent analytical choices.

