## Discussion

3

This protocol presents a comprehensive and multimodal approach to the deep phenotyping of insomnia, a condition widely recognized for its clinical and etiological heterogeneity. Conventional assessment methods, often relying on demographic data analysis (61), self-reported subjective reports (62, 63), or single-night objective metrics, have shown limited reliability and poor concordance with perceived sleep quality (64, 65). Demographic data analyses and self-reported assessments (61–63) make it difficult to capture the complexity of insomnia. Therefore, our study aims to overcome these limitations by integrating data from clinical questionnaires, continuous digital phenotyping, functional neuroimaging, and genomics to comprehensively characterize the individual experiences of insomnia.

The primary strength and novelty of this protocol are its methodological integration. By combining continuous real-world data from wearables and smartphones with laboratory neurophysiological and biological measures, we can create a dataset of unprecedented depth and breadth. This approach intentionally bridges the gap between subjective, symptom-focused, and objective sleep measurement studies. Compared to single-night laboratory polysomnography, our wearable-based monitoring provides less detail on sleep architecture but offers far greater ecological validity by sampling multiple nights in the participant’s natural environment. This design enables the capture of the dynamic and fluctuating nature of insomnia, which static, single-time-point assessments often fail to do. However, this approach is not without its limitations. The sheer volume and complexity of multimodal data require sophisticated analytical techniques and careful management to avoid false discoveries. The intensive protocol may also impose a burden on participants, and the single-center design may limit the generalizability of the findings.

Implications of this deep phenotyping approach in sleep medicine are substantial. The primary object is to support a paradigm shift from undifferentiated care to personalized management. Tailoring insomnia treatments, such as cognitive behavioral therapy for insomnia (CBT-I) or pharmacotherapy, requires recognizing biologically distinct subtypes, including those characterized by physiological hyperarousal or circadian rhythm disruption (66–68).

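### The primary fNIRS outcomes use HbO2 alone although HbR is also recorded, so a group difference in shared circulatory signal could be read as a prefrontal difference

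*Protocol article*

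**What the plan says.** All references are to the protocol article.

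- **Recording (2.6.1).** The device measures changes in "oxygenated (HbO_2_) and deoxygenated (HbR) hemoglobin concentrations", with "source-detector separations of 30 mm to ensure adequate cortical sensitivity". No shorter separation is mentioned, and none is ruled out.
- **Activation (2.6.4).** Task responses are "changes in the HbO_2_ concentration relative to the pre-task baseline", and the activation patterns "will be compared between insomnia and control groups".
- **Connectivity (2.6.4).** Pearson correlations are taken between HbO2 "time series from different prefrontal regions during both pre- and post-task resting periods". Node strength and clustering coefficients follow from them and are meant to describe how the prefrontal network is organised.
- **Preprocessing (2.8.1).** "fNIRS data undergo standard preprocessing, including motion artifact correction and signal quality assessment".
- **Analysis (2.8.7).** Established protocols in HOMER2/3, general linear models with multiplicity correction, and correlation and coherence for connectivity.
- **Covariates (2.8.2).** The ANCOVA confounders given are age, sex and comorbid conditions.
- **Arousal (Discussion).** Biologically distinct subtypes are mentioned, "including those characterized by physiological hyperarousal or circadian rhythm disruption".

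HbR appears in the description of the device and in none of the outcome definitions in 2.6.4.

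**The concern.** Light in a 30 mm channel passes through scalp and skull as well as cortex. Each channel can therefore carry a component driven by heart rate, blood pressure and scalp flow that is common to many channels. A Pearson correlation cannot tell that component from cortical coupling. Coherence has the same weakness, and multiplicity correction does not remove bias. Cross-validation gives no protection either, because a systemic difference between the groups would be reproducible.

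The article itself makes a group difference in systemic state conceivable: it names hyperarousal as a feature of one insomnia subtype, and section 2.5.3 treats resting heart rate as related to arousal and stress. If such a difference were present during the scan, it could be reported as a difference in prefrontal network organisation. It could also enter the multimodal models, since 2.6.4 says the derived neural metrics become features there. A second chromophore is already on file that could help to check this, and the outcome definitions make no use of it.

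**Working it through.** **1. The plan's own figure.** Section 2.9 states about 80% power for d ≈ 0.36 at α = 0.05 with at least 240 and 80 participants. With a two-sided test and normal approximation, SE(d) = √(1/240 + 1/80) = 0.129; 0.36/0.129 − 1.96 = 0.83, which gives power of 79.6%. The figure is reproduced and not disputed. At the enrolled 249 and 89, SE(d) = √(1/249 + 1/89) = 0.1235, and power for the same d is 83.0%.

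**2. Model for connectivity.** Write each channel as √(1 − s) × cortical signal + √s × shared systemic signal. Here s is the systemic share of HbO2 variance, taken as equal across channels, and the two parts are uncorrelated. Then

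observed r = (1 − s) × r_cortical + s.

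With the same r_cortical in both groups, the group gap is (1 − r_cortical) × (s_insomnia − s_control).

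**3. Inputs not in the article (assumed).** Systemic share 0.20 to 0.50; cortical r of 0.2 or 0.4; between-person SD of Fisher-z connectivity 0.2 to 0.4.

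**4. Illustration with cortical r = 0.2 in both groups.**

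- Share 0.20: 0.80 × 0.2 + 0.20 = 0.36.
- Share 0.30: 0.70 × 0.2 + 0.30 = 0.44.
- Fisher-z gap: atanh(0.44) − atanh(0.36) = 0.095.

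Rejection rates below are for an uncorrected two-sided 5% test at 249 and 89. The ranges in the last two columns run from a Fisher-z SD of 0.4 to one of 0.2.

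| Cortical r | Share, control vs insomnia | Observed r | Spurious d | Rejection rate |
|---|---|---|---|---|
| 0.2 | 0.20 vs 0.20 | 0.36 vs 0.36 | 0 | 5% |
| 0.2 | 0.20 vs 0.25 | 0.36 vs 0.40 | 0.12 to 0.23 | 16% to 47% |
| 0.2 | 0.20 vs 0.30 | 0.36 vs 0.44 | 0.24 to 0.48 | 49% to 97% |
| 0.4 | 0.20 vs 0.30 | 0.52 vs 0.58 | 0.22 to 0.43 | 41% to 94% |

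For a 0.10 gap anywhere in the assumed ranges, the spurious d runs from 0.22 to 0.58, on both sides of the design's 0.36.

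**5. Node strength.** If node strength is the sum of a node's correlations, a gap of 0.08 per edge becomes (k − 1) × 0.08 for k nodes.

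**6. Activation.** Let b be a person's steady systemic level, c the cortical response and e the task-evoked systemic response. Change from baseline is (b + c + e) − b = c + e. A group difference in b drops out; a group difference in e does not. If e alone shifted the group means by 0.2, 0.3 or 0.36 SD, an uncorrected test at 249 and 89 would reject 37%, 68% or 83% of the time. These shifts are also assumptions.

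**7. Limits of these rates.** Section 2.3 provides compensation for participants who complete everything except fNIRS and blood sampling. The fNIRS sample may therefore be below 338, and the rejection rates would then be lower, as they would after FDR correction.

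**The case against.** The strongest reply is that this is a condensed article. Its preprocessing list is introduced as examples, and 2.8.7 defers to established protocols, so filtering or systemic regression may well be in the full plan. That stands: the silence is weak evidence, and the point does not rest on it. It rests on outcome definitions that the article does fix on one chromophore.

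A reader might infer three stronger things, none of which the documents support.

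- *That the plan correlates signals with no prior correction.* Section 2.6.4 does not say so, and preprocessing comes first under 2.8.1.
- *That the bias favours the study's hypothesis.* No direction is stated for activation or connectivity, and the Introduction calls earlier neuroimaging findings somewhat inconsistent. Hyperarousal is named for one possible subtype, not for the whole insomnia group during the scan, and nothing says that it raises the shared fraction of HbO2 variance.
- *That any arousal difference contaminates activation.* Steady levels cancel, as shown above.

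It is also fair to say that every magnitude here is assumed, that left-right asymmetry indices are less exposed if the systemic signal is symmetric, and that the main subtype clustering in 2.8.4 is specified on digital features rather than fNIRS. These points limit the weight of the concern without removing it.

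**Conclusion.** The point holds as a modest, inexpensive improvement to a stated outcome definition. Activation, connectivity and the network measures built on it rest on HbO2 alone although HbR is available. A group difference in connectivity could therefore reflect a different systemic share rather than prefrontal organisation; for activation the same requires a group difference in the task-evoked systemic response.

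Such a difference is plausible but not shown. Its size cannot be derived from the article: the gap of 0.36 against 0.44 is an illustration under assumed shares of 0.20 and 0.30 with cortical r = 0.2 in both groups, and with equal shares the contrast has no bias. Whether a removal step already exists is open. The limitations in the Discussion cover spatial resolution and prefrontal-only coverage of fNIRS, and do not mention this one.

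**What to change.** In 2.6.4 and 2.8.7:

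1. Run the same activation and connectivity group comparisons on HbR alongside HbO2.
2. Add a sensitivity analysis with the shared component removed before task responses and correlations are computed. Use short-separation channels as regressors if they were stored, otherwise a global-signal or first-principal-component regressor. If such a step is already in the pipeline, name it; that settles this item.
3. Describe an HbO2-only group difference that neither analysis supports as possibly systemic rather than prefrontal.

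Data collection is complete, so the cost is analysis time only. HbR is noisier, so a true difference may go unconfirmed. Removing a shared component can also take out real, widespread prefrontal signal. For both reasons these should be supporting analyses that shape the interpretation, and not a gate that an HbO2 result must pass. HbR light crosses the same superficial tissue, so agreement between the two chromophores supports a cortical reading without proving it.

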### Biological sample collection

2.7

Biological sample collection and genomic analysis are integral components of the deep phenotyping approach, providing insights into the genetic predisposition and molecular mechanisms underlying insomnia heterogeneity.

#### Sample collection and processing

2.7.1

Venous blood samples (10 mL) are collected from all participants at the baseline visit using EDTA tubes to preserve nucleic acids. The blood samples are processed within 2 h of collection. The samples are centrifuged at 2000×g for 10 min at 4°C to separate the plasma from the cellular components. The buffy coat layer, which contains leukocytes rich in DNA and RNA, will be carefully extracted and aliquoted into cryovials. Plasma will be similarly aliquoted for potential biomarker analysis. All samples are labeled with unique study identification codes and stored at -80°C until analysis.

#### DNA extraction and genotyping

2.7.2

High-quality genomic DNA will be extracted from buffy coat samples using the QIAamp DNA Blood Mini Kit (Qiagen, Germany) following the manufacturer’s protocol. DNA concentration and purity will be assessed using NanoDrop spectrophotometry, with samples meeting the quality criteria (260/280 ratio 1.8-2.0, DNA concentration ≥50 ng/μL) to proceed to genotyping.

Genome-wide genotyping will be performed using the Axiom PangenomiX Array (Thermo Fisher Scientific, USA), a high-density array capable of interrogating over 600,000 genetic variants, including single nucleotide polymorphisms (SNPs) and copy number variants. This array provides a comprehensive coverage of common and rare variants across the genome, including enhanced coverage of pharmacogenomic and clinically relevant loci.

#### Polygenic risk score calculation

2.7.3

Primary genomic analysis will focus on calculating insomnia-specific Polygenic Risk Scores (PRS) rather than novel gene discovery. The PRS calculation will utilize summary statistics from the most recent and largest genome-wide association study (GWAS) of insomnia, leveraging data from over 1.3 million individuals.

PRS computation will follow established protocols:

Quality control of genotype data including removal of variants with call rate <95%, minor allele frequency <1%, and Hardy-Weinberg equilibrium p-value <1×10^−6^Linkage disequilibrium clumping using European reference panels from the 1000 Genomes ProjectPRS calculation across multiple p-value thresholds (5×10^−8^, 0.001, 0.01, 0.05, 0.1, 0.5, and 1.0) to optimize predictive performance.Standardization of PRS values (mean=0, SD = 1) for interpretability

The resulting continuous PRS variable will quantify each participant’s genetic liability for insomnia, with higher scores indicating a greater genetic predisposition.

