### Study design

2.1

This study employed a single-center prospective observational design with two parallel cohorts, an insomnia group and a normal sleeper control group. The study was conducted at the Korea University Anam Hospital in Seoul, South Korea, and DataMaker Inc. in Daejeon, South Korea, between March 2023 and October 2024. The observational nature of the study allowed for the careful assessment and monitoring of participants’ sleep patterns, behaviors, and relevant physiological and biological parameters over a 4-week period. This duration was selected to capture a representative range of day-to-day fluctuations in sleep and daytime symptoms, while minimizing participant burden. A parallel-cohort design allows for the comparison of these measures between individuals with insomnia and those with normal sleep, enabling the identification of distinguishing features and potential subtypes of insomnia. The entire study consists of a baseline visit (week 0), a 4-week monitoring period (weeks 1-4), and an endpoint visit (week 4). An overview of this protocol is shown in **Figure 1**.

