#### Specialized analyses

2.8.7

*fNIRS data analysis*: Neuroimaging data analysis will follow established protocols using HOMER2/3 software. Statistical parametric mapping identifies task-related activation patterns, whereas functional connectivity analysis utilizes correlation and coherence measures. Group comparisons will be performed using general linear models with multiple comparison correction.

*Genomic data analysis*: Polygenic risk scores will be analyzed using linear models and population stratification controls. Gene expression data will employ differential expression analysis with multiple testing corrections. Pathway analysis using Gene Set Enrichment Analysis (GSEA) will identify biological mechanisms.

*Circadian analysis*: Cosinor analysis of physiological time series will employ nonlinear least-squares fitting to extract rhythm parameters. Population-mean cosinor analysis will test group-level rhythm differences, whereas individual cosinor analysis will characterize personal circadian profiles.

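### The polygenic risk score is picked from seven p-value thresholds by predictive performance, with no tuning outcome, tuning sample or correction for the scan named; if tuned in this cohort, its test on the tuning outcome is anti-conservative

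*Protocol article*

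**What the plan says.** Section 2.7.3 makes the insomnia PRS the focus of the primary genomic analysis. It plans PRS "calculation across multiple p-value thresholds", seven in all (5×10⁻⁸, 0.001, 0.01, 0.05, 0.1, 0.5 and 1.0), the stated purpose of the grid being "to optimize predictive performance". The section then refers to one resulting continuous variable, so one score is taken from seven according to how well it predicts.

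That score is then used in three ways:
- Section 2.7.5 plans to correlate it with digital phenotypes.
- Section 2.8.7 says "Polygenic risk scores will be analyzed using linear models and population stratification controls".
- Sections 2.6.4 and 2.7.5 treat genomic data as features in computational analyses and risk prediction models.

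On ancestry, Section 2.7.3 specifies "Linkage disequilibrium clumping using European reference panels" and a discovery GWAS "leveraging data from over 1.3 million individuals", without giving the ancestry of those individuals. Section 2.1 says "The study was conducted at the Korea University Anam Hospital in Seoul, South Korea". The final step is "Standardization of PRS values (mean=0, SD = 1) for interpretability".

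**The concern.** Choosing the best of seven scores by performance and then testing it as if it were the only one makes the p-value too small and the R² too large. The article names no safeguard that reaches this step:
- Nested cross-validation (Section 2.8.5) is described for the supervised models, not for building or testing the PRS.
- The Benjamini-Hochberg correction (Section 2.8.2) acts across variables. It cannot repair a p-value already minimised over thresholds before it enters the list.
- Section 2.8.7 names multiple-testing correction for gene expression, but for the PRS only stratification control.

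At stake is the credibility of the named primary genomic analysis. There is a second route to harm. If the threshold is tuned on case status in the whole cohort before the folds are split, the outcome leaks into the nested cross-validation through the PRS feature, and performance estimates described as unbiased would not be.

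**Working it through.** **The plan's own figures.** None is given for the PRS. The general figures in Section 2.9 reproduce:
- Group difference, 240 vs 80, d = 0.36: SE = √(1/240 + 1/80) = 0.1291; 0.36/0.1291 − 1.96 = 0.83; power 79.6%.
- Correlation, N = 330: tanh[(1.960 + 0.842)/√327] = 0.154, inside the stated 0.15–0.16.

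Both assume a variable fixed in advance, so they do not cover a score picked from seven.

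**Inputs from the article.** Seven thresholds (2.7.3); α = 0.05 (2.8.8; two-sided assumed); n = 338, as 249 insomnia and 89 controls (2.9).

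**Assumption.** The correlations among the seven scores are not in the article. The scores are nested, so corr(i, j) = √(V_i/V_j), where V is the score variance and i is the stricter threshold. V depends on the GWAS architecture, so several were tried.

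**1. Upper bound.** If the seven scores were independent: 1 − 0.95⁷ = 0.302.

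**2. Best of seven, chosen and tested on the same outcome, no true association, nominal 5%.**

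| Setting (assumed) | False-positive rate |
|---|---|
| Six simulated GWAS architectures, nested scores | 15.9%, 16.7%, 18.9%, 19.1%, 19.3%, 19.7% |
| Individual-level simulation, 249/89, two architectures | 12.0%, 15.4% |
| AR(1) correlation 0.9, 0.8, 0.7, 0.5 between adjacent scores | 14.8%, 19.4%, 22.4%, 26.8% |

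The first two rows give the working range of 12–20%. The AR(1) row is a wider sensitivity range. In the pure-null architecture (19.3%) no variant passed 5×10⁻⁸, so that figure is for six scores. With the threshold fixed in advance, the individual-level simulation returns 4.8% and 5.0%.

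**3. R² under the null.** Expected value for one fixed score: 1/(338 − 1) = 0.0030. Mean best-of-seven R² in the individual-level simulation: 0.0057 and 0.0063. From the maximum z² over nested scores, divided by 338: 0.0068–0.0070. So 0.3% becomes about 0.6–0.7%. For scale, the smallest correlation that Section 2.9 aims to detect, 0.15, is an R² of 0.15² = 2.25%.

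**4. Threshold tuned on one outcome, PRS tested on another** (same six architectures):

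| Correlation of the two outcomes | False-positive rate |
|---|---|
| 0 | 4.7–5.0% |
| 0.3 | 6.3–6.8% |
| 0.5 | 8.6–9.4% |
| 0.7 | 11.5–13.2% |

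If case status is the tuning outcome, ISI is close to it by construction, since Section 2.2 defines the groups partly by ISI (15 or more against below 8). Digital phenotypes may be much less correlated.

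**5. Honest cut-off if the best of seven is reported.** In the six architectures the critical |z| is 2.47–2.55, a nominal p of about 0.011–0.013. Bonferroni gives 0.05/7 = 0.0071.

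**6. The LD panel.** Clumping uses discovery p-values and reference LD, not the outcomes of these participants. The retained variants are therefore independent of the tested outcome, and there is no type I error figure to compute. Any loss is in R² and power, and the article gives nothing from which to size it.

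**The case against.** The article does not say that the threshold is tuned in the study participants. A reader might take that as stated, but it is an inference. A condensed article can leave the tuning sample and resampling scheme to an analysis plan not shown here, and the nested cross-validation of Section 2.8.5 might be meant to include the PRS scan. Section 2.8.8 also promises appropriate multiplicity corrections. Section 2.9 disclaims formal testing of a single endpoint, and the Discussion concedes overfitting risk and the lack of external validation. This stands as far as it goes, which is why the conclusion is conditional. It does not remove the point: the article does state the selection rule, describes only one cohort, and attaches no safeguard to the scan.

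Three stronger readings are not supported:
- **All PRS associations are anti-conservative.** They are not. A test on an outcome unrelated to the tuning outcome stays near 5%.
- **European clumping makes the score invalid, shifted or poorly calibrated.** A poorly matched panel weakens a score; it does not inflate type I error. Standardisation removes a cohort-wide mean shift, no absolute-risk calibration is claimed, and stratification control is planned. A European panel may also be the right match if the discovery GWAS is mainly European; the article does not say. Section 2.1 gives a place of recruitment, not participant ancestry.
- **The multiplicity plan counts one PRS test instead of seven.** No section counts PRS tests either way.

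**Conclusion.** The point holds in conditional form. Followed as written, with tuning in the only cohort described, the PRS test on the tuning outcome rejects a true null about 12–20% of the time instead of 5%, and null R² about doubles. The exact size depends on the assumed correlations among the nested scores, so the range should be quoted and not a single figure. Inflation fades as the tested outcome moves away from the tuning outcome. Leakage into the nested cross-validation arises only if tuning on case status precedes the split into folds.

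The ancestry point is separate and secondary. With the discovery ancestry unstated and portability to this cohort not discussed among the limitations, describing the score as each participant's genetic liability claims more than the method secures. A null result could reflect poor transfer of the score and should not be read as absence of genetic vulnerability.

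This should be corrected before the genomic analysis. It affects that analysis and models that take the PRS as a feature, not the study as a whole.

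**What to change.** In Section 2.7.3, replace the in-sample optimisation with one of the following:
- **One pre-stated score**: a single fixed threshold, or the first principal component of the seven threshold scores. Neither uses the outcome, so the nominal 5% is restored.
- **A nested choice**: select the threshold inside the inner cross-validation folds, and base association tests on a permutation p-value that repeats the whole seven-threshold scan in every permutation.

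Under the second option, name the tuning outcome and sample. Under either, state that no PRS choice uses case status outside the training folds when the PRS enters a classifier.

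For the secondary point, state the discovery ancestry, justify the LD panel against it, and qualify the liability wording, noting that the score may predict less well in this cohort.

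The cost is some extra computing on existing genotypes, with no new participants or samples. The downside is a smaller reported R². Section 2.7.3 is written in the future tense, so the change can be made before the scores are tested if that work has not begun.
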